### Predicting cognitive intervention response with machine learning: spatiotemporal maps and feature definition

To identify if EEG measures can be used to predict response to the compensation and adaptation therapies, we will use machine learning techniques to classify individual patients that benefit from the compensation and adaptation therapies (responders) from patients who do not improve after the compensation and adaptation therapies (non-responders). Machine learning will be implemented using the Pattern Recognition for Neuroimaging Toolbox (PRoNTo) [23] with features from the whole-brain spatiotemporal analysis. First, we will create three-dimensional spatiotemporal images from averaged ERP data. A three-dimensional matrix (32 × 32 × 81) corresponding to the scalp electrode space and time points will be constructed, per participant for the different conditions. The images will be smoothed at full width half maximum of 12 mm × 12 mm × 20 ms. Before conducting the machine learning, we will perform the standard spatiotemporal mass-univariate general linear model analysis. A full factorial analysis will be performed to examine the spatiotemporal changes after the therapy programmes, with the following factors: volatility (stable and volatile), treatment (CCT or CIRCuiTS), and visit (baseline, 12 and 24 weeks). All statistical maps will be thresholded at *p* < 0.05 family-wise error (FWE) corrected for multiple comparisons.

Next, we will conduct the machine learning analysis, and the three-dimensional spatiotemporal images will be fed as features into the classifier. To classify the compensation and adaptation therapy responders and non-responders, class labels will be assigned to each participant. In PRoNTo, we will apply the support vector machine (SVM) and Gaussian process algorithms [24], which has shown to be effective in classifying schizophrenia patients using neuroimaging features [12]. The SVM training phase involves assigning weights to features and finding the hyperplane that maximises the margin between the groups of participants; the sign of the total feature weights multiplied by the test sample will determine the classification of participants. A *k*-fold cross-validation scheme will be conducted, dividing the group of participants into *k* subgroups, and iteratively assigning subgroups for training or testing until all subgroups have been through the testing. Mean-centering will be performed on all models and normalisation will be applied. In order to attain statistical measures, permutation tests will be performed (1000 repetitions) for each model and cross-validation scheme. To correct for multiple comparisons, we will apply false discovery rate correction of *q* = 0.05. Model sensitivity and specificity will be determined using the receiver operating characteristic curve, which will show the true positive rate (sensitivity) as a function of false positive rate (1 − specificity). The area under the curve will determine how well we are able to differentiate between compensation and adaptation therapy responders and non-responders using the best classifier from the EEG data.

Finally, we will conduct regression modelling to examine model performance by comparing true compensation and adaptation therapies’ response with that response predicted by the model. Spatiotemporal images for each subject will be mapped to their BACS scores, and machine learning regression algorithm—Kernel Ridge Regression [25, 26]—will be trained to predict these scores. To determine the accuracy of predicted response to compensation and adaptation therapies, we will calculate mean-squared error, Pearson’s correlation, and coefficient of determination statistics. Again *k*-fold cross-validation will be applied, permutations will be conducted to attain statistical measures, and multiple comparisons will be Bonferroni corrected.

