### Eligibility criteria

The specified inclusion criteria are as follows: (1) aged between 18 and 65 years (inclusive), (2) fulfilling the clinical diagnosis of DSM-V criteria for schizophrenia spectrum disorder, (3) absence of uncorrected sensory impairments, (4) English literacy skills greater than grade 4 as per years of education, and (5) agreement to participate, with capacity to consent and able to follow the study instructions and procedures.

The specific exclusion criteria are as follows: (1) presence of substance dependence (with the exception of tobacco), (2) intellectual handicap (estimated using the Test of Premorbid Functioning (TOPF)), (3) people who are unable to understand or communicate in English or with English literacy skills less than grade 4 as per years of education, and (4) comorbid physical illnesses that would impair the participants’ ability to complete the trial.

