### Outcomes

A battery of validated clinical measures will be conducted at baseline, at post-treatment, and at 3-month follow-up. Raters who are blind to the randomisation of condition (registered psychologists) will complete the measures. The assessors instruct the participant not to reveal their group allocation.

The following measures will be used:
Brief Assessment of Cognition in Schizophrenia (BACS) [17] is an instrument that assesses the aspects of cognition found to be most impaired and most strongly correlated with outcome in patients with schizophrenia. This is the primary outcome measure.Test of Premorbid Functioning (TOPF) [18] is a test of premorbid intelligence as estimated from reading ability.Subjective Scale to Investigate Cognition in Schizophrenia (SSTICS) [19]. This measures the perception of cognitive abilities when completing everyday tasks.Social Functioning Scale (SFS) [20] assesses areas of functioning that are crucial to the community maintenance of individuals with schizophrenia.Brief Psychiatric Rating Scale (BPRS) [21] is a widely used scale for measuring symptom severity of patients with schizophrenia.Electroencephalography (EEG). Participants will listen to a duration auditory oddball paradigm while their brain responses are measured with EEG. An auditory oddball paradigm consists of presentations of sequences of predictable sound stimuli (standard sounds) that are infrequently interrupted by unpredictable sound stimuli (deviant sounds). Sounds will be delivered via headphones and will vary in duration. All tones will be presented in a sound range that is comfortable for the participants. In the “volatility” auditory oddball task, the participants will be asked to pay attention to the sounds in order to judge the proportion of different sound types and rate their confidence on this judgement. This will allow us to assess the ability of participants to learn the statistical relationships of sound types, as well as the confidence on their own judgement. Prior to the experiment, the participants will be familiarised with the different sound types and trained with two short practice tasks. Participants will make responses using a computer keyboard and a mouse. The duration of the practice task will be 2 min, and the duration of the volatility auditory oddball task will be approximately 18 min, with a total duration of testing of approximately 20 min per participant, including breaks.

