### Recruitment

Participants will be recruited through the public mental health community clinics. Participants will continue to receive standard clinical care for the duration of the study. Medication prescribed at baseline will be collected and any changes noted. Participants will not be compensated for their time spent in treatment or assessment sessions.

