## Discussion

Compensation and adaptation therapies have been demonstrated to improve neurocognitive functioning in people with schizophrenia spectrum disorders. The current study aims to evaluate the equivalence of two different compensation and adaptation therapies (CIRCuiTS and CCT) within a community mental health service. This study also aims to identify if mismatch negativity can predict an individual’s response to compensation and adaptation therapies. This knowledge will allow clinicians to identify individuals who are more likely to receive benefit from a compensation and adaptation therapy programme.

This RCT has several strengths. To date, no other study has incorporated neurophysiological measures of mismatch negativity to identify participants that may be more likely to benefit from compensation and adaptation therapies. This is a novel approach and may assist with identifying future participants of compensation and adaptation therapy programmes. Participants will be randomly assigned to each group, and the raters remain blind to condition to avoid bias. A variety of outcome measures will be used to assess functioning across neurocognitive, social, and neurophysiological domains.

No formal assessment of inter-rater reliability will be conducted. Groups will be matched for total exposure to therapy (2 h per week over 12 weeks). Participants in the CIRCuiTS group may not have completed all 40 phases prior to the post-intervention assessments. Clinician effects may influence the results as one therapist will deliver CCT and one will deliver CIRCuiTS.

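### The EEG prediction models are tested only against chance, with no baseline BACS term or reference model, so the Discussion's claim of clinical usefulness would not be supported even by a positive result

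*Protocol article*

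**What the plan says.** The Protocol article's section on predicting intervention response with machine learning sets out the features, the test and the performance measures.

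- **Features.** For classification, "the three-dimensional spatiotemporal images will be fed as features into the classifier". No clinical or demographic feature is named.
- **Test.** "In order to attain statistical measures, permutation tests will be performed (1000 repetitions) for each model and cross-validation scheme". The null hypothesis of such a test is that EEG and response are unrelated.
- **Performance.** The area under the curve is reported "using the best classifier from the EEG data", with no comparator.
- **Regression.** "Spatiotemporal images for each subject will be mapped to their BACS scores", and the fit is presented as the accuracy of predicted response. The visit is not named, nor whether the score is a change, and no baseline BACS term appears.

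Other baseline information is available. Under Outcomes, "A battery of validated clinical measures will be conducted at baseline, at post-treatment, and at 3-month follow-up"; the measures listed there include BACS, TOPF, SSTICS, SFS and BPRS. Under Recruitment, "Medication prescribed at baseline will be collected and any changes noted". Age is needed to apply the eligibility criterion "aged between 18 and 65 years (inclusive"), although it is not listed separately as a collected variable.

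The Discussion draws the practical conclusion: "This knowledge will allow clinicians to identify individuals who are more likely to receive benefit".

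**The concern.** Beating chance shows that EEG is associated with response. It does not show that EEG tells anyone more than the baseline assessments do. If the EEG images partly reflect baseline cognition, and baseline cognition is related to the outcome, an EEG-only model can succeed purely as a stand-in.

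The regression is the most exposed part. A participant's post-treatment BACS score depends strongly on the baseline score, so anything correlated with baseline BACS will appear to predict it. The classifier is exposed too. Its labels rest on reliable change in cognition, and change is itself correlated with the baseline score whenever test–retest correlation is below 1.

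What is at stake is the conclusion in the Discussion and the Background's rationale for EEG, which is more precise information on who would respond. The primary comparison of CCT with CIRCuiTS is not affected.

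**Working it through.** **Inputs from the protocol.** Up to 100 participants and 15–20% dropout (Sample size). 100 × (1 − 0.20) = 80, which reproduces the stated figure of approximately 80 completers; 15% dropout gives 85. The protocol states no figure for the prediction analysis.

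**Assumed inputs (not in the protocol).** The correlation between EEG and the baseline measure, the BACS test–retest correlation, the responder share, and how well the baseline measure predicts response. One ready-made EEG score stands in for the learned model. In every scenario EEG carries no information beyond the baseline measure.

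**1. Regression, post-treatment BACS as target.** Let r be the EEG–baseline BACS correlation and ρ the test–retest correlation. The EEG–outcome correlation is then c = r × ρ. The probability of a significant one-sided 5% test is about 1 − Φ(1.645 − atanh(c) × √(80 − 3)).

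| r | ρ = 0.7 | ρ = 0.9 |
|---|---|---|
| 0.2 | c = 0.14, 34% | c = 0.18, 48% |
| 0.3 | c = 0.21, 59% | c = 0.27, 78% |
| 0.4 | c = 0.28, 81% | c = 0.36, 95% |

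Simulation agrees to within about one percentage point. With baseline BACS in the model, the test for EEG rejects in about 5% of the same trials. At r = 0 the unadjusted rate is also about 5%.

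**2. Regression, change in BACS as target.** With equal variances at the two visits, baseline and change correlate at −√((1 − ρ)/2), which is −0.387 at ρ = 0.7 and −0.224 at ρ = 0.9. The EEG–change correlation has size r × 0.387 or r × 0.224. For r = 0.2 to 0.4 this runs from 0.045 to 0.155, and the same formula gives 10% to 39%. A change score reduces the problem but does not remove it.

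**3. Classifier.** Simulation with N = 80, 1,000 trials per setting, a one-sided permutation test of AUC with 1,000 permutations, 30% or 50% responders, and a baseline score whose own AUC is 0.65 to 0.75. Here r is the within-group correlation of EEG with that score. The last column is a likelihood-ratio test of EEG added to the baseline score.

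| r | Mean EEG AUC | EEG-only test significant | EEG added to baseline score significant |
|---|---|---|---|
| 0 | 0.50 | 4–6% | 4.3–7.2% |
| 0.3 | 0.54–0.58 | 13–33% | 4.6–7.2% |
| 0.5 | 0.57–0.63 | 29–65% | 4.5–7.9% |
| 0.7 | 0.61–0.68 | 46–90% | 5.1–6.5% |

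**4. Effect of having to learn the EEG score.** The plan must learn weights from 32 × 32 × 81 images. In a check with a 10-fold cross-validated kernel ridge classifier and the signal spread over 10, 50 or 500 independent features, pass rates fell to 5–20%, against 17–64% for a ready-made score in the same data. Smooth, correlated EEG features could raise that. The planned false discovery rate and Bonferroni corrections, left out of all the calculations above, would lower it.

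**The case against.** The strongest reply is that the planned test answers the stated aim. The Objectives ask whether baseline MMN can predict who might benefit, not whether it adds to clinical measures, and the Abstract promises only a contribution to emerging evidence. That stands: the EEG-only analysis is legitimate and should stay. It does not rescue the Discussion's sentence about clinicians, which is worded without condition and goes further than a test against chance can support.

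A second reply is that a comparator may sit in an analysis plan that is not shown. That is possible. But the article describes this analysis down to smoothing kernel and permutation count, and it fixes the features, the test and the conclusion. The mismatch between them is on the page.

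Three stronger readings are tempting and are not supported:

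- A reader might infer that EEG adds nothing. The documents give no correlation between EEG and any baseline measure, so this is unknown.
- A reader might infer that services already hold the competing information. The protocol describes the cognitive and functional measures as trial assessments by blinded raters; it does not say that clinics have them.
- A reader might take the percentages above as false-positive rates of the planned test. They are not. In those scenarios EEG is truly associated with response, through the baseline measure, so the test is right about association. What would be wrong is reading it as added value.

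**Conclusion.** The concern holds in a limited form. As written, a positive EEG result could not be told apart from EEG standing in for baseline cognition or another collected baseline measure, and the Discussion's claim would not follow from it. The regression is the clearest case: about 34–95% of trials significant with zero added value if the target is post-treatment BACS, r is 0.2 to 0.4 and ρ is 0.7 to 0.9. The figures are illustrative. They rest on assumed correlations and a ready-made EEG score, fall to about 5% when EEG is unrelated to the baseline measures, and would be lower for a model that must learn its weights. The point should be fixed, but it concerns an additional aim and leaves the primary analysis untouched.

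**What to change.** In the machine-learning section:

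1. Keep the EEG-only classifiers and regression as planned.
2. State that the regression target is change in BACS, or post-treatment BACS with baseline BACS in the model. The second is safer, because change remains correlated with baseline.
3. Fit, in the same folds, a small pre-specified reference model from baseline data already collected: baseline BACS first, with few others such as BPRS and age.
4. Report cross-validated AUC and R-squared for the reference model alone and for reference plus EEG, with a permutation test of the EEG part.

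In the Discussion, make any claim of added clinical value conditional on that gain. Settle this before response labels are analysed.

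The cost is a little more analysis and no new data. The real limitation is precision. With about 80 completers and, at an assumed 20% responder share, 0.20 × 80 = 16 responders, the estimated gain will be imprecise. That is why the reference model should be small, and why a null gain must not be read as proof that EEG adds nothing.

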### Data management

Researchers from Metro South Addiction and Mental Health Services will be responsible for data entry and analyses. Researchers from the Queensland Brain Institute will have access to the deidentified database to enter EEG data and perform analyses. Participants will be allocated a number to allow for their data from each time point to be linked for analyses.

A screening log will be utilised to track potential participants and record the number of individuals approached, consented, meeting inclusion/exclusion criteria, withdrawals, and completion (in keeping with standard CONSORT diagram requirements). Hard copies of the questionnaires, clinical assessments, and measures will be sent to the clinical co-ordinator and retained in a secure room, in a locked filling cabinet. The trial coordinator will be responsible for entering data into the password-protected database. The researchers will conduct the data analyses.

### Protocol amendments

Any amendments to the protocol will be submitted to the appointed HREC by the Chief Investigator for approval. Any approved amendments by the appointed HREC will be forwarded by the Chief Investigator for submission to the appropriate Research Governance Offices. If a protocol amendment requires changes to the informed consent form, the revised form will be approved by the reviewing ethics committees and site governance officers.

### Dissemination policy

Results will be disseminated in peer review publications and published international journals. Only deidentified data will be reported. Results will be provided to participants on their request.

## Discussion

Compensation and adaptation therapies have been demonstrated to improve neurocognitive functioning in people with schizophrenia spectrum disorders. The current study aims to evaluate the equivalence of two different compensation and adaptation therapies (CIRCuiTS and CCT) within a community mental health service. This study also aims to identify if mismatch negativity can predict an individual’s response to compensation and adaptation therapies. This knowledge will allow clinicians to identify individuals who are more likely to receive benefit from a compensation and adaptation therapy programme.

This RCT has several strengths. To date, no other study has incorporated neurophysiological measures of mismatch negativity to identify participants that may be more likely to benefit from compensation and adaptation therapies. This is a novel approach and may assist with identifying future participants of compensation and adaptation therapy programmes. Participants will be randomly assigned to each group, and the raters remain blind to condition to avoid bias. A variety of outcome measures will be used to assess functioning across neurocognitive, social, and neurophysiological domains.

No formal assessment of inter-rater reliability will be conducted. Groups will be matched for total exposure to therapy (2 h per week over 12 weeks). Participants in the CIRCuiTS group may not have completed all 40 phases prior to the post-intervention assessments. Clinician effects may influence the results as one therapist will deliver CCT and one will deliver CIRCuiTS.

## Data Availability

On completion of this study, the dataset will be made available from the corresponding author on reasonable request.

## Abbreviations

ANCOVA: Analysis of covariance
ANOVA: Analysis of variance
ANZCTR: Australian New Zealand Clinical Trials Registry
BACS: Brief Assessment of Cognition in Schizophrenia
BPRS: Brief Psychiatric Rating Scale
CIRCuiTS: Computerised Interactive Remediation of Cognition–Training for Schizophrenia
CCT: Compensatory Cognitive Training
CONSORT: Consolidated Standards of Reporting Trials
DSM-V: Diagnostic and Statistical Manual of Mental Disorders-Fifth Edition
EEG: Electroencephalography
FWE: Family-wise error
HREC: Human research ethics committee
IQ: Intelligence quotient
MMN: Mismatch negativity
MMRM: Mixed-effects model repeated measures
NDCT: National Database for Clinical Trials Related to Mental Illness
PRoNTo: Pattern Recognition for Neuroimaging Toolbox
RCT: Randomised controlled trial
SAS: Statistical Analysis System
SFS: Social Functioning Scale
SSTICS: Subjective Scale to Investigate Cognition in Schizophrenia
SVM: Support vector machine
TMG: Trial management group
TOPF: Test of Premorbid Functioning
